### Outcome assessment

Measures of feasibility, safety and adherence will be collected throughout the study. Outcomes related to ED symptoms, general psychopathology and neurocognition will be measured before and after the study intervention to assess treatment success. Each assessment session will be split into an in-person visit and at-home component to accommodate time constraints and minimise disruption to task performance due to participant fatigue. The in-person assessment measures will take between 75 - 150 minutes to complete, and the online questionnaires will take approximately 30 minutes.

### Outcome measures

#### Feasibility outcomes

As this is a feasibility study, an extensive range of outcome measures are included to help determine which are most sensitive to detecting a treatment effect. This will enable us to determine primary outcome(s) for a future large-scale RCT. However, based on previous research,^49^ the Eating Disorder Examination Questionnaire (EDE-Q) is anticipated to be a key outcome measure.

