If given concurrently (ie, ‘online training’), NIBS is reported to boost the effects of cognitive training on the reduction of cognitive biases and the improvement of response inhibition.^63^ NIBS may enhance synaptic strength in neuronal pathways activated by cognitive training, amplifying effects of training and thus cognitive bias modification efficacy.^64^ As the effectiveness of tDCS may thus be improved by pairing administration with a cognitive task inducing activity in the target brain region,^65–67^ such combined treatment interventions have been investigated among alcohol dependent inpatients (ABM and tDCS),^68^ and to enhance inhibitory control related to food consumption (Go/No-Go Task and tDCS).^65^ The insignificant findings from these studies warrant commentary that to date, studies that have found positive effects of tDCS have either included obese participants or have had multi-session protocols.^65 69–71^ As this study incorporates both aspects, it is optimally designed to yield significant results.

In light of both the individual and societal burden incurred by the rising prevalence of BED and obesity, research interventions informing treatments that lead to stable and long-lasting remission are of critical importance, and novel therapies may play a role in serving as adjuncts to treatment as usual (TAU), to enhance improvement in clinical outcomes obtained from engaging with ED treatment services. This research trial is the first to combine two promising novel intervention strategies in an integrated treatment and will yield important findings to shape future clinical trials. The intervention conditions of this feasibility study will involve six sessions of concurrent ABM and real or sham tDCS over 3 weeks, and will assess participant acceptability and dropout rates at this treatment frequency and duration. Additionally, the frequency of participants’ ED symptoms and other outcomes related to general psychopathology and neurocognition will be measured before and after the study interventions to assess treatment success. In summary, this proof-of-concept and feasibility study will establish the utility of concurrent ABM+real tDCS in improving clinical outcomes in participants with BED, compared with ABM+sham tDCS, and a wait-list control group.

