## Study aims

In line with established recommendations for outcomes of feasibility trials,^72^ which at present are supported by the National Institute for Health Research, the primary aim is to assess the feasibility of using concurrent ABM+real tDCS compared with concurrent ABM+sham tDCS as a potential adjunct to TAU in this patient population, and acquire key information to inform the development of a large-scale RCT.

The specific objectives of the proposed feasibility study are to:

Establish the feasibility of conducting a large-scale RCT of ABM+tDCS in patients with BED by assessing recruitment, attendance and retention rates.Determine the practicality of administering both ABM and tDCS simultaneously.Determine the best instruments for measuring outcomes in a full trial by examining the quality, completeness and variability in the data.Estimate the treatment effect sizes and SD for outcome measures to inform the sample size calculation for a large-scale RCT.Evaluate whether the treatment is operating as it is designed by analysing process measures, such as within-session Visual Analogue Scales (VAS) of key ED symptoms.Determine whether patients with BED evaluate concurrent ABM+tDCS as acceptable and credible.Obtain information about patients’ willingness to undergo random allocation to ABM paired with either real or sham tDCS administration, or the wait-list control condition.

A secondary aim is to investigate the potential efficacy of concurrent delivery of both forms of treatment on BED.

This will involve evaluating if:

Concurrent sessions of ABM+real tDCS are superior to ABM+sham tDCS and to wait-list control in terms of frequency of objective binge eating episodes, food cue reactivity, food craving, food intake, ED psychopathology and mood.Concurrent ABM+tDCS is superior to the two other conditions in having an effect on the targeted neurocognitive mechanism (approach bias for high calorie food) and related neurocognitive parameters (ie, impulsivity, delayed gratification, emotional regulation).Concurrent ABM and sham tDCS is superior to the wait-list control in eliciting therapeutic effects on the aforementioned clinical outcomes and neurocognitive mechanisms, yet demonstrates an efficacy level below that of concurrent ABM and real tDCS.

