### Data analysis

Data will be analysed with the Statistical Package of Social Sciences (SPSS) version 26. Feasibility outcome data will be analysed with appropriate summary statistics. To determine quality, completeness and variability of the clinical outcome data, descriptive statistical analyses and graphical methods will be used. Intent-to-treat analyses will be performed. The size of the treatment effect on each outcome measure will be the difference in outcome data between those in the two treatment conditions and control condition at post-assessment and follow-up. Group differences will be estimated using linear mixed effects regression models, controlling for the baseline level of the outcome. The goal here is not to determine significant group differences but to establish a suitably precise effect size for the primary outcome at the post treatment assessment. This estimate will be used to guide the sample size of a future efficacy trial. Correlational analyses may be computed to analyse relationships between outcome variables and influences of potential covariates such as demographic variables (ie, gender, age, BMI and clinical variables), that is, start/stopping of psychotherapy, psychotropic medication and presence of comorbidities. Outcome data already obtained for participants who discontinue or deviate from the intervention protocol will be kept and analysed.

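### The protocol lets the future primary outcome be chosen by observed treatment effect and sizes the next trial from the same data, so the planning effect can be biased upward; the precision claimed for it is unsupported

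*Protocol article*

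**What the plan says.** Under Outcome measures (Feasibility outcomes) the protocol article explains that "an extensive range of outcome measures are included to help determine which are most sensitive to detecting a treatment effect", and continues: "This will enable us to determine primary outcome(s) for a future large-scale RCT". It adds that, on the basis of earlier research, "the Eating Disorder Examination Questionnaire (EDE-Q) is anticipated to be a key outcome measure". Approach bias assessment tasks and the Discussion use the same idea of looking for the most sensitive measure.

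Study aims gives a different basis for choosing instruments: "Determine the best instruments for measuring outcomes in a full trial by examining the quality, completeness and variability in the data". A separate objective there is: "Estimate the treatment effect sizes and SD for outcome measures to inform the sample size calculation for a large-scale RCT".

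Sample size says the study is meant to supply effect sizes for powering later studies. It justifies the target of 60 completers by the sample size at which estimates of the SD settle down.

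Data analysis disclaims significance testing as the goal. The goal is instead "to establish a suitably precise effect size for the primary outcome at the post treatment assessment", and "This estimate will be used to guide the sample size of a future efficacy trial". The article does not say which clinical measure that primary outcome is.

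**The concern.** In this trial, sensitivity to a treatment effect can be judged only from the observed differences between arms. If a measure is promoted because its observed difference is large, that difference contains favourable chance error as well as any true effect. Using the same estimate to size the next trial carries the error forward: the planned sample is too small and the real power falls below the nominal figure.

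Nothing in the article blocks this route. Data analysis leaves its primary outcome unnamed, the EDE-Q is only anticipated as a key measure, and no single contrast among the three arms is singled out. No confidence limit, shrinkage, external estimate or important difference is mentioned as a safeguard.

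A second, independent point is precision. A sample size justified by stability of the SD says little about how well a between-arm difference is estimated.

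**Working it through.** **Inputs from the protocol article**
- Sample size: 60 completers, attrition 0.10, 66 recruited, 22 per arm. Randomisation: 1:1:1.
- Table 1, repeated outcome instruments: EDE-Q, Go/No-Go, SST, delay discounting, food choice, food challenge, taste test, F-AAT and SRC (9), plus 10 questionnaires, giving 19. Adding BMI gives 20, before subscales or within-session scales.
- Data analysis: mixed models adjusted for baseline.

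**Assumptions (not in the article):** correlation between measures rho from 0 to 0.7; baseline correlation r of 0 or 0.5 (also 0.7 for precision); true d of 0.3; next trial planned at two-sided 5% and 80% power.

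**Plan's own figure.** 60/(1 − 0.10) = 66.7, so 67 against the stated 66, which agrees closely enough. Conversely 66 × 0.9 = 59.4 completers, or about 20 per arm.

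**Precision of one prespecified outcome.** SE(d) = sqrt(2/n) × sqrt(1 − r²), with n = 20 per arm and sqrt(2/20) = 0.316.

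| r | 95% half-width |
|---|---|
| 0 | 1.96 × 0.316 = 0.62 |
| 0.5 | 0.62 × 0.866 = 0.54 |
| 0.7 | 0.62 × 0.714 = 0.44 |

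Unadjusted, an observed d of 0.5 has a 95% CI of about −0.12 to 1.12. With n per arm = 2(1.96 + 0.84)²/d² = 15.68/d², the point estimate implies 63 per arm and the upper limit 13. The lower limit lies below zero and implies no usable size.

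**Selection, upper case.** Simulation (100,000 replicates) of the largest of 20 estimates when all 20 measures share the same true effect, 20 per arm:

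| rho | mean inflation of d, r = 0 | r = 0.5 |
|---|---|---|
| 0 | 0.59 | 0.51 |
| 0.3 | 0.49 | 0.43 |
| 0.5 | 0.42 | 0.36 |
| 0.7 | 0.32 | 0.28 |

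The entries scale as they should: 0.59 × sqrt(1 − 0.7) = 0.32, and 0.32 × 0.866 = 0.28.

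**Selection between two candidates.** Inflation = 0.564 × 0.316 × sqrt(1 − rho), unadjusted. This is 0.18 at rho 0 and 0.10 at rho 0.7.

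**One score fixed in advance.** Inflation from selection is zero.

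**Consequence in the upper case.** If every true d is 0.3, the trial needs 15.68/0.09, about 175 per arm. The selected estimate averages 0.62 to 0.89 unadjusted, which gives a planned 41 down to 20 per arm and real power of 27% down to 16%. With r = 0.5 it averages 0.58 to 0.81, which gives 47 down to 24 per arm and power of 31% down to 18%.

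**Milder version.** If true effects differ (mean 0.3, SD 0.15), selection does find a better measure, with true d of 0.42 to 0.50. Its estimate is still 0.70 to 0.95, and real power is 24% to 52%.

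**The case against.** A reader might infer that the plan ranks some 20 measures and takes the one with the largest effect. The article does not say so. The measures are there to help decide, more than one primary outcome is allowed for, and Study aims gives criteria that do not depend on the arms at all. Those criteria could sit beside sensitivity rather than contradict it. Where the article applies the sensitivity idea concretely, it compares two tasks for one construct, approach bias. The maximum of 20 is therefore an upper case, and several of the 20 are mechanistic measures unlikely to become primary.

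The EDE-Q is anticipated as a key outcome on external grounds. If it is carried forward whatever the results, there is no selection across instruments. Which EDE-Q score is used is a detail that an article may leave to a fuller document. Data analysis also does not say that its primary outcome is the one chosen under Feasibility outcomes, and it speaks of guiding, not fixing, the next sample size.

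These points remove the claim that the plan prescribes picking the winner, and they lower the size. They do not remove the concern that the text permits it: the sensitivity criterion and the reuse of effect sizes are both stated, and the EDE-Q is not committed to.

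A reader might also infer that an effect would be reported for some measure even if none exists. The objective covers effect sizes for outcome measures generally, nothing says only the best will be shown, and the article says replication in a larger trial is needed. The Introduction's remark that "it is optimally designed to yield significant results" is loose wording about population and number of sessions, not an analysis rule, and carries no weight here.

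**Conclusion.** The concern holds in a limited form. The article allows the future primary outcome(s) to be chosen by observed sensitivity to treatment and uses effect sizes from the same participants for planning, without naming the outcome whose effect is carried forward. The possible upward bias in d runs from zero (one EDE-Q score fixed in advance), through about 0.10 to 0.18 (two candidates), to an upper case of about 0.28 to 0.59 (largest of 20 equally effective measures). These figures rest on the assumed correlations and on 20 completers per arm; the power figures also rest on the assumed true effects.

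The precision claim fails on its own terms, whatever is done about selection. A 95% half-width of 0.44 to 0.62 SD comes from the sample size, and fixing the outcome in advance does not narrow it.

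This is worth correcting before analysis but is not critical. The harm falls on a later, separately designed trial.

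**What to change.** 1. In Data analysis, name one EDE-Q score and one between-arm contrast as the only effect carried forward, and do so before any unblinded analysis.
2. In Feasibility outcomes, choose the other instruments on quality, completeness and variability pooled over arms, in line with Study aims, and not on observed group differences.
3. Replace the precision claim with the expected 95% half-width: about 0.62 SD unadjusted, 0.54 at baseline correlation 0.5, 0.44 at 0.7.
4. State that the next trial will be sized from the pilot SD and an externally set important difference, not from the observed effect. With 60 completers the 95% limits for the SD are about 0.85 to 1.22 times its estimate, so this is the quantity the pilot can supply.

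The cost is wording only, with no added participants or visits. The downside is that the next trial's planned size will look larger.

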#### Intervention/service related outcomes

Feasibility outcomes include recruitment, attendance and retention rates, and acceptability of treatment by participants. Patients’ acceptance of study interventions will be assessed by measuring treatment dropout rates and via the treatment tolerance and acceptability questionnaires. An interview assessment of treatment experience will be conducted with 20 participants after the follow-up is completed. Ten participants from each intervention group will be invited to provide feedback on their initial expectations and experiences of the ABM+real/sham tDCS treatments, perceived strengths and weaknesses of the treatment they received, and suggestions for improvements in procedures. Interviews will be recorded, transcribed and analysed using thematic analysis. This will allow future studies to consider patients’ feedback in the development of research and clinical protocols of concurrent ABM and tDCS.

#### Clinical outcomes

##### ED and related psychopathology

###### Eating Disorder Examination Questionnaire

EDE-Q^83^ is a widely used measure of eating-disordered behaviour and is widely regarded as the instrument of choice for the assessment of EDs. This will be administered at baseline, post-assessment and follow-up.

###### Body mass index (kg/m^2^)

This assessment of body composition provides accurate estimates of body fat percentages in adults, where sex and age are factored into the analysis measuring height and weight.^84^ To calculate BMI, height and weight measurements will be obtained by the researcher at baseline, post-assessment and follow-up as part of the EDE-Q.

###### Approach bias assessment tasks

To identify the most sensitive method of assessing change in approach bias towards high-calorie food items, two different computerised measures of approach bias will be used. In the Food Approach-Avoidance Task (F-AAT)^85^ participants are shown colour photographs of high-calorie, palatable foods such as chocolate, cake and pizza, and non-food household and office items such as sponges and stationary on a computer screen.^86^ They are instructed to approach and avoid these stimuli by moving a joystick toward themselves (approach) or away from themselves (avoidance). In the Stimulus Response Compatibility Task,^87^ participants perform a symbolic movement by making a manikin image walk toward (approach) or away from stimuli (avoidance). See online supplementary appendix C for more detailed information. Both of these tasks will be administered at baseline, post-assessment and follow-up.

###### Food choice attitudes/behaviour

The Food Choice Task^88–90^ is a computer-based paradigm that measures responses to images of foods to assess food attitudes and characteristics of eating behaviour. Participants rate images of food on a computer screen according to healthiness as well as tastiness. Based on these ratings they are then offered a choice between a food that they consider ‘neutral’ and a series of other foods. See online supplementary appendix C for more detailed information. This task will be performed at baseline and post-assessment.

###### Food craving after cue exposure task

The Food Challenge Task^41^ will be used to examine cue-induced food craving. In this task, participants rate their state food craving using the Food Cravings Questionnaire State Version^91 92^ before and after being presented with a video on a computer screen of foods shown to be highly appetising.^93^ See online supplementary appendix C for more detailed information. This task will be performed at baseline and post-assessment.

###### Trait food craving

Three questionnaires will be used to comprehensively assess mechanisms implicated in trait food craving. The Food Cravings Questionnaire Trait Version–reduced^94^ is a 15 items only reduced version of a self-report questionnaire that measures trait levels of craving for food. The 21-item Power of Food Scale^95^ scale assesses the psychological influence of the mere presence or availability of food. It measures appetite for, rather than consumption of, palatable foods, at three levels of food proximity (food available, food present and food tasted). The Yale Food Addiction Scale Version 2.0^96^ reflects the current diagnostic understanding of addiction to further investigate the potential role of an addictive process in problematic eating behaviour.^75 97–101^ See online supplementary appendix C for more detailed information. Each of these scales will be administered at baseline, post-assessment and follow-up.

###### Food intake in a bogus taste test

During the bogus taste test,^102^ participants will be instructed to rate and optionally consume highly palatable high-calorie food items presented in three bowls. See online supplementary appendix C for more detailed information. This task will be performed at baseline and post-assessment.

###### Preference for immediate versus delayed rewards

The Delay Discounting Task with Money and Food^103^ examines whether small amounts of food would be discounted more steeply than money, as occurs with larger amounts. See online supplementary appendix C for more detailed information. The Delayed Gratification Inventory assesses participants' ability/tendencies to delay gratification for five domains (food, physical pleasures, social interactions, money and achievement^104^). Both task and questionnaire will be administered at baseline, post-assessment and follow-up.

###### Inhibitory control

The cued Go/No-Go computer task is a classic test of executive function, requiring effortful response inhibition and measures impulse control by the ability to inhibit instigated, prepotent responses. A food specific go/no-go task^105^ measures impulsivity and response inhibition with respect to food and non-food items. The Stop Signal Task (SST)^106^ measures inhibitory control. Participants are required to engage in a computer task but withhold their response in the presence of a stop signal. An adaptation of the food version of the SST^107^ will facilitate a comparison of responses between food and non-food categories. See online supplementary appendix C for more detailed information. Both of these tasks will be performed at baseline, post-assessment and follow-up.

##### Mood and emotion regulation

The Emotion Regulation Questionnaire^108^ is designed to measure respondents’ tendency to regulate their emotions regarding cognitive reappraisal and expressive suppression. The Positive and Negative Affect Schedule^109^ measures the degree of positive or negative affect experienced “right now” in the current study. The Depression, Anxiety and Stress Scale^110^ evaluates mood, anxiety and stress levels over the previous week. See online supplementary appendix C for more detailed information. All of these measures will be administered at baseline, post-assessment and follow-up.

##### Within session measures

Within each training session, that is, immediately before and after the ABM+real/sham tDCS procedure the researcher will administer paper-based VAS assessing current hunger, feeling of fullness, urge to eat, urge to binge eat, feeling low, level of tension, level of stress, level of anxiety and any discomfort due to tDCS and ABM in the training session. See online supplementary appendix C for more detailed information.

### Intervention

In both intervention groups, participants will receive six sessions of concurrent ABM and real or sham tDCS which will be delivered twice a week for 3 weeks. A researcher trained in tDCS administration will deliver the training sessions.

#### Rationale for number of sessions

Treatment parameters for interventions of ABM and tDCS separately in psychiatric disorder research have not yet been standardised and vary from 1 to 12 sessions across a timeframe of days to multiple weeks. Mixed results regarding optimal frequency of ABM sessions and related forms of cognitive bias modification has been reported.^111^ A maximum accumulative effect of modification efficacy at six sessions has been found for ABM for alcohol dependence.^44^ While there is a similar paucity of specifications for treatment parameters within tDCS, multi-session NIBS interventions are significantly more effective at reducing cravings and strengthening the ability to refrain from food consumption than single-session protocols in EDs and obesity.^112^ As a single session of tDCS on patients with BED was found to reduce craving and caloric intake,^59^ it was hypothesised that repeated administration of tDCS would enhance this effect and may decrease binge eating frequency.

